**Discussion:**

This study will be the first clinical trial to examine the effects and safety of MHM on intracranial compliance measured by non-invasive monitoring. Limitation includes the impossibility of blinding the physical therapist who will supervise the interventions. It is expected with this study to demonstrate that MHM can improve respiratory mechanics and hemodynamic parameters and provide a safe intervention with no changes in intracranial compliance in stroke patients.

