## Methods

### Trial design

The protocol complies with a randomized controlled equivalence trial, double-blinded, parallel (1:1 ratio), and exploratory approved by the Research Ethics Committee of the Hospital de Clínicas of the Universidade Federal do Parana (CAAE: 01,378,118.7.0000.0096). The individuals are allocated through simple randomization into two groups. All items in the Data Set of the Register of Tests by the WHO were recorded on the database of the Brazilian Clinical Trial Registry (RBR – 5qs9k2n). Any alteration in the protocol is informed to the above-mentioned bodies. When preparing this protocol, we used the SPIRIT reporting guidelines [17], and a table with the standard protocol items (SPIRIT) is presented in Table 1. The SPIRIT checklist is available as an additional file (Additional file 1).

**Table 1 Tab1:** Time schedule of enrollment, interventions, assessments, and visits for participants according to Recommendations for Interventional Trials (SPIRIT)

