**Secondary outcome measures**								
Respiratory mechanics	Static compliance			X	X	X	X	X
	Dynamic compliance			X	X	X	X	X
	Resistance			X	X	X	X	X
	Expired current volume							
Hemodynamic stability	MAP			X	X	X	X	X
	HR			X	X	X	X	X
	SpO_2_			X	X	X	X	X

*TTP* time to peak, *MAP* mean arterial pressure, *HR* heart rate, *SpO*
_*2*_ peripheral oxygen saturation

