In scenarios of normality of ICP and ICC, there is a proportion between the peaks, where P1 > P2. However, in situations of abnormality, there is a change in the morphology of the ICP waveform, with an increase in ICP associated with a low ICC, with P2 > P1. For the TPP variable, the higher the value found, the greater the chance of the peak being P2, which also corresponds to a decrease in the ICC [22, 23].

In this study, the evaluations will be carried out in five (T1–T5) moments:T0: start monitoring, the interval between T0 and T1 is intended to ensure patient stabilization for the start of data collection;T1: capture initial patient data;T2: assess whether the MHM protocol had effects on ICC;T3: verify whether aspiration combined with MHM could lead to different effects on outcomes;T4 and T5: check whether there was stabilization of parameters related to ICC and respiratory mechanics.

The moment of evaluation T2 is the most relevant for the primary outcome; as for the secondary outcomes, evaluations from T2 to T5 are the most relevant.

Data will be collected through a monitor and analyzed using the Brain4care Analytics System, considering that at a time interval, the software selects an average of pulses to form the waves.

To capture the data, the ICP assessment sensor will be chosen according to the cranial circumference (S, M, L, XL) considering as protocol the lowest sensor possible with reading, following the manufacturer’s recommendations. Data collection will start after the coupling procedure and confirmation by the assessor of reading compatible with the acceptable ICP curves.

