### Secondary outcomes

#### Respiratory mechanics

Respiratory mechanics is calculated at all times and for both groups by measuring the variables provided by the MV, which will allow inferring indirectly the efficiency of the maneuvers in promoting bronchial hygiene [7, 8].

The MV parameters will be adjusted according to the predicted weight for each patient [24]. Patients will be ventilated on the volume-controlled assisted mode. The following variables will be recorded: programmed parameters (Vt, PEEP, RR, V, FIO_2_) and variables related to respiratory mechanics [Ppeak, Pplateau, drive pressure, expired current volume, PIF, PEF], which along with the programmed parameters will be applied to calculate resistance (Re), static compliance (StaC), and dynamic compliance (DynC) [25].

StatC, DynC, and Re are clinical variables often used to assess the therapeutic effects of the bronchial hygiene maneuvers [7, 8, 26]. Such effect is possibly related to the recruitment of collapsed lung areas, increase in collateral ventilation, lung areas with a high time constant, and removal of secretions [8].

This protocol will use the following mathematical equations:Predicted body weightMale: 50 + 0.91 × (height in centimeters – 152.4)Female: 45.5 + 0.91 × (height in centimeters – 152.4)Resistance (Re)Re = (Ppeak – Pplateau)/VStatic compliance (StaC)StaC = VT/(Pplateau – PEEP)Dynamic compliance (DynC)DynC = VT/(Ppeak – PEEP)

We will follow a method of flow interruption at the end of the inspiration with a pause of 3 s to calculate the respiratory mechanics. Three measures will be performed using the average of the two measures with the lowest standard deviation. Upon absence of plateau, the measure will be disregarded [8].

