### Statistical methods

The collected data will be organized on a spreadsheet and summarized using techniques of descriptive statistical analysis. The qualitative variables will be summarized by building frequency tables and the quantitative variables by calculating the descriptive measures (average, mean, standard deviation, and percentiles 25–75).

The evaluations’ primary outcome and secondary outcomes will be made in 5 different times; for that, the data will be analyzed by analysis of variance (ANOVA) two-way for repeated measures with the Tukey post-test for results that present normal distribution and homogeneity of variances, verified by the test of Shapiro–Wilk and Average in Levene, respectively.

We will be using the statistical software Statistical Package for the Social Sciences (SPSS) (IBM—version 22) to analyze the collected data. Our research hypotheses will be tested using non-parametric methods. Wilcoxon test with Kruskal–Wallis post-test will also be applied (intergroups). The level of significance established was *p* ≤ 0.05. The evaluation of results and data analysis will be carried out by an independent professional.

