With this study, we expect to demonstrate the safety of performing hyperinflation maneuvers under a mechanical ventilator in critical neurological patients, proving to be a respiratory physiotherapy resource that can be used in clinical practice and provide benefits to respiratory mechanics without jeopardizing the neurological function.

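### The expected demonstration of better respiratory mechanics has no key contrast: three measures at four times share one p ≤ 0.05, with no correction across measures

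*Protocol article*

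**What the plan says.** **The claim.** The Abstract's Discussion paragraph states: "It is expected with this study to demonstrate that MHM can improve respiratory mechanics and hemodynamic parameters". The main Discussion ends by expecting a technique that will "provide benefits to respiratory mechanics without jeopardizing the neurological function". The Introduction also makes respiratory mechanics part of the objective.

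**The label.** Trial design describes a "randomized controlled equivalence trial, double-blinded, parallel (1:1 ratio), and exploratory" study.

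**The measures.** Outcome measures lists respiratory mechanics and hemodynamic stability as secondary and ranks nothing within them. Under Respiratory mechanics: "StatC, DynC, and Re are clinical variables often used to assess the therapeutic effects of the bronchial hygiene maneuvers". Table 1 marks these three at T1 to T5. It also lists expired volume, but with no marked time.

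**The times.** The Intracranial compliance section singles out T2 for the primary outcome, but "as for the secondary outcomes, evaluations from T2 to T5 are the most relevant". It also gives the times roles: T3 looks at aspiration combined with the maneuver, and T4 and T5 check for stabilization.

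**The tests.** Statistical methods names a two-way repeated-measures ANOVA with a Tukey post-test where normality and equal variances hold. It then says that the research hypotheses will be tested non-parametrically, with between-group rank tests. "The level of significance established was *p* ≤ 0.05". It mentions no adjustment on the rank-test route and no correction across measures on either route.

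**The concern.** Improved respiratory mechanics is a superiority claim, and it is the reason to use the maneuver if intracranial compliance proves unaffected. The primary outcome has a named time. The benefit claim has neither a named measure nor a named time. With twelve between-group comparisons open and none in front, the report can choose afterwards which one represents the benefit. A chance result on one measure at one time could then support a clinical recommendation.

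The wording also conflicts with itself. An exploratory study can describe respiratory mechanics without error control, but it cannot then say that it has demonstrated an improvement.

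**Working it through.** The protocol states no overall error rate for the secondary outcomes, so there is no figure of its own to reproduce. Its only relevant figure is the 0.05 threshold.

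**Inputs from the protocol:** 3 measures (Respiratory mechanics; Table 1); 4 times, T2 to T5 (Intracranial compliance); level 0.05 (Statistical methods); 30 patients per group (Sample size).

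**Assumptions:** two-sided tests, since sidedness is not stated, so 0.025 per comparison in the favourable direction; no true effect; a common correlation r between test statistics, varied over 0, 0.5 and 0.8.

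**Count:** 3 × 4 = 12. Restricting to T2 and T3, because T4 and T5 are described as stabilization checks, gives 3 × 2 = 6.

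**Independent tests:** the chance of at least one false positive is 1 − (1 − α)^k.
- k = 12: 1 − 0.95^12 = 0.46; favourable direction 1 − 0.975^12 = 0.26.
- k = 6: 1 − 0.95^6 = 0.26.
- k = 3: 1 − 0.95^3 = 0.14.

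**Correlated tests:** with c = 1.96, the chance is 1 − ∫ φ(u) [Φ((c − √r·u)/√(1−r)) − Φ((−c − √r·u)/√(1−r))]^k du. For the favourable direction the second Φ term is dropped.

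| Comparisons | Direction | r = 0 | r = 0.5 | r = 0.8 |
|---|---|---|---|---|
| 12 (T2 to T5) | two-sided | 0.46 | 0.32 | 0.19 |
| 12 (T2 to T5) | favourable | 0.26 | 0.16 | 0.09 |
| 6 (T2 and T3) | two-sided | 0.26 | 0.21 | 0.14 |
| 6 (T2 and T3) | favourable | 0.14 | 0.10 | 0.07 |
| 3 (one controlled test per measure) | two-sided | 0.14 | 0.13 | 0.10 |

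The two-sided benchmark is 0.05 and the favourable one is 0.025.

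**Sensitivity to the correlation structure:** t-tests were simulated with 30 per group. Correlations between measures and between times were set equal and multiplied where a pair differs in both. The 12 comparisons gave 0.36, 0.27 and 0.15 two-sided at correlations 0.5, 0.7 and 0.9, and 0.18, 0.13 and 0.07 in the favourable direction.

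**ANOVA route:** if Tukey holds each measure at 5% over its times, three measures remain uncorrected against one another. That is the last row of the table, 0.10 to 0.14. If Tukey instead spans all 2 × 5 = 10 group-by-time cells of a measure, the studentized-range critical value corresponds to about p = 0.0016 per pair. The 12 between-group comparisons then total at most about 1 − (1 − 0.0016)^12 = 0.02. The protocol does not say which use of Tukey is meant.

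**The case against.** Several points on the other side are sound.

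- **No decision rule.** A reader might infer that the protocol lets one significant comparison prove benefit. It does not say so; the Abstract and Discussion state expectations. The rates above apply only if the results are read that way. Nothing in the text prevents that reading, however.
- **Tukey is named.** A reader might infer that all 12 comparisons are tested at an unadjusted 0.05. That fits only the non-parametric route. A reader might also infer that the error is inflated on every route, but Tukey over ten cells gives about 2%.
- **The count can be inflated.** Adding expired volume would give 16 comparisons, but Table 1 marks no time for it. Treating T4 and T5 as equal chances to show benefit strains their stated role. Even so, six comparisons still give 0.14 to 0.21 two-sided at the assumed correlations.
- **Direction.** Only favourable results support benefit, which halves the correlated two-sided figures. It also halves the benchmark, to 0.025.
- **Exploratory label and unseen analysis plan.** Ordering of secondary outcomes is often left to an analysis plan, and the exploratory label does cover the secondary outcomes. As a complaint about a missing multiplicity plan alone, the point would fail. It stands on what the article itself states: T2 to T5 given equal standing, one threshold, and a benefit that is to be demonstrated in a study labelled exploratory.

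**Conclusion.** The concern holds in limited form. The article expects to demonstrate a respiratory benefit without naming the contrast that would show it, and neither analysis route states a correction across the three measures.

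On the non-parametric route, which is the one said to test the research hypotheses, reading any one of 12 comparisons as benefit gives a false favourable result about 0.09 to 0.16 of the time against 0.025, roughly four to six times nominal. On the ANOVA route the excess is smaller, and it disappears for the between-group comparisons if Tukey covers all ten cells.

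The correlations and two-sidedness are assumptions, and the size depends on them. The documents do not support saying that a false claim of benefit is built into the plan, or that 0.46 is the expected rate. The point affects how the secondary claim may be worded and leaves the primary comparison untouched.

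**What to change.** Before outcome data are examined, amend the Intracranial compliance and Statistical methods sections in one of two ways:

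1. Name one key respiratory-mechanics contrast between groups, adjusted for T1, at two-sided 5%. Static compliance at T3 is one example. The sponsor may prefer another measure or time, provided that it is fixed in advance.
2. Apply Holm across the three measures at one named time. The smallest p-value is then compared with 0.05/3 = 0.0167, and the overall rate stays at or below 5%.

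Report the other measures and times with confidence intervals, labelled exploratory. Limit the language of demonstration and benefit in the Abstract and the Discussion to the controlled contrast. Testing it only after the primary conclusion is optional.

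The cost is wording only, with no new patients or measurements. The downside is that an isolated significant result on another measure or time can no longer be presented as a demonstrated benefit.

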### Secondary outcomes

#### Respiratory mechanics

Respiratory mechanics is calculated at all times and for both groups by measuring the variables provided by the MV, which will allow inferring indirectly the efficiency of the maneuvers in promoting bronchial hygiene [7, 8].

The MV parameters will be adjusted according to the predicted weight for each patient [24]. Patients will be ventilated on the volume-controlled assisted mode. The following variables will be recorded: programmed parameters (Vt, PEEP, RR, V, FIO_2_) and variables related to respiratory mechanics [Ppeak, Pplateau, drive pressure, expired current volume, PIF, PEF], which along with the programmed parameters will be applied to calculate resistance (Re), static compliance (StaC), and dynamic compliance (DynC) [25].

StatC, DynC, and Re are clinical variables often used to assess the therapeutic effects of the bronchial hygiene maneuvers [7, 8, 26]. Such effect is possibly related to the recruitment of collapsed lung areas, increase in collateral ventilation, lung areas with a high time constant, and removal of secretions [8].

This protocol will use the following mathematical equations:Predicted body weightMale: 50 + 0.91 × (height in centimeters – 152.4)Female: 45.5 + 0.91 × (height in centimeters – 152.4)Resistance (Re)Re = (Ppeak – Pplateau)/VStatic compliance (StaC)StaC = VT/(Pplateau – PEEP)Dynamic compliance (DynC)DynC = VT/(Ppeak – PEEP)

We will follow a method of flow interruption at the end of the inspiration with a pause of 3 s to calculate the respiratory mechanics. Three measures will be performed using the average of the two measures with the lowest standard deviation. Upon absence of plateau, the measure will be disregarded [8].

#### Hemodynamic stability

The variables of MAP, HR, and SpO_2_ are used in intensive care to assess the hemodynamic impact of respiratory physiotherapy maneuvers [8].

For MAP and HR, we will consider as significant alterations either an increase or decrease by 20 mmHg or 20 bpm, respectively, while for SpO_2_, we will consider values below 90% during the application of the maneuvers [27].

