### Interventions

After the assessments, the selected patients are randomly allocated into two groups (Fig. 1): experimental group (EG)—composed of individuals who will be subjected to MHM + tracheal aspiration—and control group (CG)—only tracheal aspiration intervention. All individuals will be positioned on dorsal decubitus at the bedside at 30°; MV is adjusted on assisted ventilation mode, controlling volume, tidal volume (Vt) of 6 ml/Kg of predicted weight, positive expiratory-end pressure (PEEP) 8 cmH_2_O, inspired oxygen fraction (FIO_2)_, peripheral oxygen saturation (SpO_2_) of 94%, and respiratory rate (RR) and flow (V) adjusted to maintain ventilation synchrony and gasometric demands. We will use a number 14 closed aspiration system with verified cuff pressure and the occurrence of leaks. All participants will be subjected to tracheal aspiration, and only 2 h later, the data collection is initiated (Fig. 2). During these 2 h, patients will only be monitored and maintained on the initial position; no concomitant procedures or disconnection of MV circuit are conducted. In case it is not possible to maintain such conditions, the collection is suspended and started again at the appropriate moment. According to Robba et al. (2016), PEEP of 8 does not cause effects on ICP [20].

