### Experimental group

We will perform ventilation adjustments to proceed with the MHM. The patient will be maintained on dorsal decubitus at the bedside at 30°, on assisted ventilation mode, and controlled volume. Vt will be increased by 150% based on ideal tidal volume; square wave V; inspiratory time (Ti) equal to 1.5 s, adjusted to a peak of inspiratory flow (PIF) lower than the peak of expiratory flow (PEF); RR of 14 irpm, reduced in case of auto-PEEP; PEEP 8 cmH_2_O; FIO_2_ minimum of SpO_2_ of at least 94%. These parameters will be preserved for 10 min. The MV alarms will be adjusted to allow the safety of the maneuver; in addition, in case of Ppeak above 40 cmH_2_O or plateau pressure (Pplateau) above 30 cmH_2_O, the maneuver is immediately interrupted and the previous parameters reestablished. The hyperinflation maneuver will not be associated with any other bronchial hygiene maneuver.

After 10 min, the recommendations of the American Association for Respiratory Care [21] (2010) will be applied in the aspiration procedure, suggesting that the patients are ventilated with FIO_2_ at 100% for 30 s before and 60 s after the procedure to avoid hypoxemia. In this study, each patient will be subjected to tracheal aspiration for 15 s for three consecutive times through a closed aspiration system with catheter number 14. Subsequently, the ventilation parameters will be readjusted according to the initial parameters.

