### Outcome measures

Primary outcomes will consist of the alterations in ICC indicated in the morphology analysis of the ICP wave due to the MHM since in critical neurological patients, it is crucial to control the secondary lesion and complications caused by the need for MV. Secondary outcomes will range from respiratory mechanics and hemodynamic stability.

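### SpO2 at T2 and T3 is compared between arms without the FIO2 in force, so a null result at those times is not evidence of safety

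*Protocol article*

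**What the plan says.** **The outcome.** The Outcome measures section states: "Secondary outcomes will range from respiratory mechanics and hemodynamic stability". Table 1 schedules SpO2 at T1 to T5 in the hemodynamic group. The Hemodynamic stability section introduces it this way: "The variables of MAP, HR, and SpO_2_ are used in intensive care to assess the hemodynamic impact of respiratory physiotherapy maneuvers". The one criterion given is a desaturation flag: "for SpO_2_, we will consider values below 90% during the application of the maneuvers".

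**The analysis.** Statistical methods sends the primary and secondary outcomes at five times to two-way repeated-measures ANOVA, with non-parametric tests as well. SpO2 is therefore compared between arms as a measured value, besides being flagged below 90%. The Primary outcome section names T2 to T5 as the most relevant times for secondary outcomes.

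**The FIO2 rules.** Three statements bear on the reading:
- Interventions, initial settings for both arms: FIO2 is followed in the list by "peripheral oxygen saturation (SpO_2_) of 94" percent.
- Experimental group, during the maneuver: "FIO_2_ minimum of SpO_2_ of at least 94%. These parameters will be preserved for 10 min". The Control group section has the controls monitored only over this interval.
- Experimental group, around suction: patients are "ventilated with FIO_2_ at 100% for 30 s before and 60 s after the procedure", after which the initial parameters are restored.

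**What is recorded.** The Respiratory mechanics section includes FIO2 among the ventilator settings to be captured: "The following variables will be recorded: programmed parameters (Vt, PEEP, RR, V, FIO_2" and so on. No outcome combines it with SpO2, and no adjustment for it is stated.

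**The concern.** SpO2 depends on both the lungs and the oxygen supplied. When the supply is chosen to reach an SpO2 target, or is set to 100% for a procedure, part of any change in gas exchange moves out of SpO2 and into FIO2. An outcome that looks only at SpO2 then loses that part.

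The times most exposed are T2 and T3, both among those the protocol calls most relevant for secondary outcomes. At T2 the FIO2 rule has just been restated for one arm only. At T3 the reading follows suction, when oxygen has just been at 100%.

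The Abstract expects improved hemodynamic parameters and a safe intervention, and SpO2 sits in the hemodynamic group. A finding of no SpO2 difference at T2 or T3 could be offered in support of safety when it partly reflects the oxygen given. An oxygenation gain could be missed for the same reason.

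**Working it through.** The protocol gives no figure that depends on this point, so there is none to reproduce. The check sets the FIO2 rules against the reading times, then shows by arithmetic what raw SpO2 can conceal.

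**Step 1. FIO2 at each reading**

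| Time | FIO2 according to the text | Can raw SpO2 mask a difference? |
|---|---|---|
| T1 | Initial settings, both arms | Starting point for the comparison |
| T2 | Experimental arm: lowest FIO2 meeting the 94% floor, or initial value if already restored. Control arm: no change stated | Yes, if FIO2 differs from T1 or between arms |
| T3 | 100% for the first 60 s after suction, then initial settings | Yes, if read in or just after those 60 s |
| T4, T5 | Initial settings | Little, if settings were restored |

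The T2 row has two possibilities because the text does. Interventions has the maneuver arm return to baseline values after the 10 minutes. Experimental group mentions the return to initial parameters only after suction.

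**Step 2. Share of T3 on 100% oxygen.** Inputs: 60 s after suction (Experimental group) and a 5-minute T3 stage (Interventions).

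60 s / 300 s = 0.20, or 20% of the stage.

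This is a share of the stage. The text does not say whether SpO2 at T3 is a spot reading or an average, or at what minute it is taken. If oxygen stays at 100% through the three 15 s suction passes (an assumption), the whole step lasts 30 + 3 × 15 + 60 = 135 s.

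**Step 3. Distance to T4 and T5.** Counting 10 and 20 minutes from the end of suction:
- T4: 600 − 60 = 540 s, or 9 minutes after the oxygen step ends.
- T5: 1,200 − 60 = 1,140 s, or 19 minutes after it ends.

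**Step 4. What an unchanged SpO2 can conceal.** The protocol gives no FIO2 values, so those below are assumptions, as is SpO2 = 95%, chosen just above the floor. Formula: ratio = SpO2 / FIO2; change = ratio / 316.7 − 1.

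| Assumed FIO2 | SpO2/FIO2 | Change from 0.30 | Change in SpO2 |
|---|---|---|---|
| 0.30 | 95 / 0.30 = 316.7 | reference | none |
| 0.35 | 95 / 0.35 = 271.4 | −14% | none |
| 0.40 | 95 / 0.40 = 237.5 | −25% | none |
| 0.45 | 95 / 0.45 = 211.1 | −33% | none |

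If FIO2 does not change, the ratio and raw SpO2 move in proportion and nothing is hidden. The problem therefore exists only where FIO2 differs between the readings or arms being compared.

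**The case against.** **SpO2 is a stability variable.** The secondary domains are respiratory mechanics and hemodynamic stability. Benefit to the airways is to be inferred from compliance and resistance, and the stated SpO2 criterion is a desaturation flag. This stands in part: the protocol does not present SpO2 as an oxygenation efficacy endpoint. But SpO2 is also scheduled at five times and sent to between-arm tests, so a null comparison will be produced and read.

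**FIO2 is not titrated throughout.** A reader might infer that an arm whose gas exchange worsens is steadily given more oxygen, that an improving arm is weaned, and that SpO2 will look equal whatever the maneuver does. The documents do not support this. Maneuver settings are kept for 10 minutes, initial settings are then restored, and no continuous adjustment or weaning is described. The 94% during the maneuver is a floor and does not hold SpO2 at that value. A fall at fixed FIO2 would show. This objection stands in full and confines the point to T2 and T3.

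**The oxygen step is short and probably common to both arms.** Controls are to be suctioned as the experimental arm is, so the step need not favor either arm. That is fair. However, a shared step can still lift both arms and shrink a real difference at T3.

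**FIO2 is already recorded, and the sizes are illustrative.** Both are true. Recording FIO2 makes the remedy cheap, but the stated outcome still ignores it. No document figure shows that FIO2 would move by the amounts in the table.

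**Conclusion.** The point holds in a limited form. SpO2 is compared between arms without regard to FIO2. At T2 it can mask a difference in oxygenation if FIO2 then differs from T1 or between arms. At T3 it can do so if read during or just after 100% oxygen. A null SpO2 result at those two times should not be taken as evidence of safety.

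The size cannot be fixed from the protocol. Under the assumed FIO2 range, a 14% to 33% lower SpO2/FIO2 would leave SpO2 unchanged. At T3, 20% of the stage falls on 100% oxygen.

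The conclusion rests on two conditions that the text leaves open: whether FIO2 is actually changed for the maneuver, and when within T2 and T3 SpO2 is read. It does not reach T4 and T5 if initial settings are restored. Nor does it affect intracranial compliance as the primary outcome, or the sample size of 60. It is a modest weakness in one secondary outcome, worth correcting because the correction is nearly free.

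**What to change.** Amend the Hemodynamic stability section and the SpO2 row of Table 1 as follows:
- Analyse SpO2 at T1 to T5 together with the FIO2 recorded at the same moment, for example with SpO2/FIO2 as a supplementary derived variable.
- State that the T3 SpO2 reading is taken once FIO2 is back at its pre-suction setting. State also when within T2 the reading is made.
- Keep SpO2 below 90% as the safety event, read from raw SpO2 as now.
- Reconcile Interventions and Experimental group on when the maneuver arm returns to initial settings, so that the FIO2 in force at T2 is clear.

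The cost is some wording, one derived variable from data already collected, and a fixed reading time at T2 and T3. No ventilator or oxygen setting changes. One small drawback is that SpO2/FIO2 discriminates poorly when SpO2 is near 100%, so it should accompany raw SpO2 and not replace it.
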